### Statistical analysis

Descriptive statistics will be used to summarize baseline characteristics. Baseline characteristics will be examined for any statistically significant differences between randomized groups. Such variables will be used as covariates in an adjusted analysis. The primary analysis will follow the intention-to-treat principle (ITT) [40] whereby all participants that drop out of the study or are otherwise lost-to-follow-up will be classified as still smoking. The primary analysis will compare the proportions of patients in each group (group A vs group B) to achieve smoking cessation using Pearson’s chi-square test. Additional analysis will employ logistic regression to adjust for variables known to be strongly associated with smoking cessation, including but not limited to age, sex, and psychiatric comorbidities.

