#### Sample size calculations

The anticipated absolute continuous abstinence rate for group A (weeks 9 to 12) for the primary outcome measure is set at 45%. This is based on the quit rates reported for combination NRT (nicotine patch and short-acting NRT) [16]. Trials of combination NRT were used to inform this estimate because: (1) randomized trials of a high-dose nicotine patch are not available to inform the projected treatment size, and (2) similar to nicotine patch, combination NRT also allows upward titration to reach satiety. It is anticipated that the abstinence rates for an active titrated nicotine patch will at least meet, if not exceed those of combination NRT. The estimated continuous abstinence rates during weeks 9 to 12 for group B are 30% based on published literature of the effects of a standard nicotine patch in clinical trials [41]. Assuming *p* = .05, a sample of 163 per group provides 80% power to detect this difference at weeks 9 through 12. With an estimated 20% quit rate during the 2-week run-in period, we therefore plan to recruit approximately 500 participants into the trial until we have 400 eligible for randomization. Randomized groups of 200 participants per group will ensure that the group is adequately powered for longer-term outcomes as well. Since we are using ITT, all participants randomized to a treatment arm will be included in the analysis so our *n* will remain constant and our power to detect a difference between groups should not be significantly affected by loss to follow-up as long as it is more or less equal in the two arms. Our overall proportion of participants defined as quit will decrease but the difference between the two groups should remain the same.

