## Discussion

Fixed doses of NRT can be ineffective for many patients as the given dose can exceed some individuals’ level of tolerance to nicotine while for others it may be an inadequate dose that fails to sufficiently quell withdrawal and cravings [23]. By personalizing doses of NRT, clinicians may be able to assist individuals on either end of the dosing spectrum. The aim of this study is to understand the efficacy of 10 weeks of personalized dosing of a nicotine patch in motivated smokers unable to quit after 2 weeks of a standard nicotine patch (21 mg). The study optimizes the current evidence-based practice for smoking cessation treatment (NRT with brief behavioral counseling) using a personalized dosing approach. Given the pragmatic nature of the study and the heterogeneity of the participants, the results from this study will be externally valid and will be applicable to a wide variety of healthcare settings.

The challenges encountered to date with the implementation of this investigator-initiated study have been primarily related to the lack of ready access to matching placebo patches that satisfy the safety and manufacturing requirements of clinical trial regulators in Canada. In addition, although the design is pragmatic to include those with psychiatric or substance use comorbidities, trial burden (weekly visits, adherence to the protocol) might make retention problematic for these participants. Concurrent cannabis smoking and alcohol consumption could affect the primary outcome and the outcome measure had to be chosen to limit false positives.

Given the strong link between smoking, cancer, and cardiovascular disease and evidence that quitting smoking at any age diminishes this risk, even small increases in absolute quit rates can have a substantial population-level impact on reducing the incidence of smoking-related disease, mortality rates, and associated healthcare costs.

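### The assurance that loss to follow-up leaves the A–B difference and power intact does not follow from scoring every dropout as a smoker

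*Protocol article*

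**What the plan says.** Under Statistical analysis, the protocol article compares groups A and B by Pearson's chi-square test under the intention-to-treat label, with one rule for missing outcomes: "all participants that drop out of the study or are otherwise lost-to-follow-up will be classified as still smoking".

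Under Sample size calculations, the planning rates are 45% for A ("The anticipated absolute continuous abstinence rate for group A (weeks 9 to 12) for the primary outcome measure is set at 45" per cent) and 30% for B ("The estimated continuous abstinence rates during weeks 9 to 12 for group B are 30" per cent). The requirement is given as "a sample of 163 per group provides 80% power to detect this difference at weeks 9 through 12", and 200 per arm will be randomized. The same section says that power "should not be significantly affected by loss to follow-up as long as it is more or less equal in the two arms". It closes by saying that the overall quit proportion will fall but the difference between the groups should not change. No loss rate is given for either arm. The article does not say whether the 45% and 30% already count dropouts as smokers.

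**The concern.** If nobody who is lost would have been abstinent, scoring them as smokers is correct and the quit proportion does not fall. If the proportion does fall, some of those scored as smokers would have counted as quitters. In that case the number of quitters removed from each arm depends on that arm's loss, and a difference in loss becomes part of the estimated treatment effect.

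The direction cannot be known in advance. Higher loss in A would hide a real benefit, and higher loss in B would create or inflate one. The article gives reasons why loss could differ. The Background says that a dose may exceed tolerance in some people and be too low to relieve withdrawal in others. Only group A receives active patches above 21 mg, while group B stays on the active dose with which all randomized participants failed to quit. At stake is whether a positive result shows more quitting rather than better retention, and whether a null result shows no benefit.

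**Working it through.** **Inputs.** From the article: 45% v 30%; α = 0.05 (taken as two-sided); 200 per arm; Pearson's chi-square; dropouts scored as smokers. Assumed, because the article does not give them: loss in each arm and true abstinence among those lost.

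**1. The plan's own figure.** With pooled variance and no continuity correction,

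n = [1.96·√(2 × 0.375 × 0.625) + 0.8416·√(0.45 × 0.55 + 0.30 × 0.70)]² / 0.15² = 162.3, so 163 per group.

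The stated 163 is reproduced. Power at 200 per arm is 87.5%.

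**2. What the rule does.** Let p be an arm's true abstinence rate, d its loss, and q the true abstinence rate among those lost. The observed rate is p − d·q, so

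observed difference = (pA − pB) − (dA·qA − dB·qB).

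- If q = 0 in both arms, nothing changes, and the quit proportion does not fall either.
- If loss is equal and those lost are abstinent equally often in both arms, the proportions fall and the difference is kept. For example, 20% loss with q = 30% in both arms gives 39% v 24%, still 15 points.
- If loss is equal and those lost resemble their own arm (q = p), the difference shrinks by the factor 1 − d.
- If loss is unequal and q > 0, the difference is in general biased.

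So a fall in the quit proportion with an unchanged difference needs a second condition, equal abstinence among those lost, which the article does not state.

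**3. No true effect, 30% abstinent in both arms.** Results are exact binomial enumeration of the two-sided 5% Pearson test, 200 per arm. For dropouts abstinent as often as stayers, the observed rate is 0.30(1 − d). For dropouts half as likely as stayers, the stayers' rate is 0.30/(1 − 0.5d) and the observed rate is that times (1 − d).

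| Loss in the two arms | All dropouts smoke | Half as likely: observed, type I error | Equally likely: observed, type I error |
|---|---|---|---|
| 20% v 20% | 5.0% | equal rates, 5.0% | 24.0% v 24.0%, 5.0% |
| 10% v 15% | 5.0% | 28.4% v 27.6%, 5.4% | 27.0% v 25.5%, 6.3% |
| 10% v 20% | 5.0% | 28.4% v 26.7%, 6.8% | 27.0% v 24.0%, 10.5% |
| 10% v 25% | 5.0% | 28.4% v 25.7%, 9.3% | 27.0% v 22.5%, 18.1% |
| 15% v 30% | 5.0% | 27.6% v 24.7%, 10.0% | 25.5% v 21.0%, 18.7% |

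Which arm has the higher loss does not alter the total. It decides which arm the false positives favour.

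**4. True 45% v 30%, read as rates before dropouts are scored as smokers.** Here q is set as a fraction of the arm's own true rate.

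| Loss A / B | q | Observed A v B | Difference | Power |
|---|---|---|---|---|
| none | – | 45.0% v 30.0% | 15.0 points | 87.5% |
| any | 0 | 45.0% v 30.0% | 15.0 points | 87.5% |
| 20% / 20% | half the arm's rate | 40.5% v 27.0% | 13.5 points | 82% |
| 20% / 20% | the arm's rate | 36.0% v 24.0% | 12.0 points | 75% |
| 20% / 10% | half the arm's rate | 40.5% v 28.5% | 12.0 points | 72% |
| 20% / 10% | the arm's rate | 36.0% v 27.0% | 9.0 points | 49% |

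**The case against.** The rule is stated in advance, is the same for both arms and fits the endpoint. Abstinence has to be confirmed by CO at in-person visits and by urinary anabasine at week 13, so a person who has left cannot meet it. This stands, and the rule should stay primary.

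A reader might infer that unequal loss by itself raises the false-positive rate to 11–18%. The documents do not support that. With no abstainers among those lost, the error rate is 5.0% for any gap. The higher figures need a gap of 10 to 15 points and dropouts who abstain as often as stayers, and the article gives neither. The mechanisms also point away from that extreme. People who leave for lack of relief are probably still smoking. Table 1 adds patches only for participants who report smoking, so those on high doses are not a random sample of quitters. Dose reduction and blinding may limit differential loss, and the pressures in the two arms may partly cancel.

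The Discussion remark that trial burden "might make retention problematic for these participants" might be read as predicting unequal loss. It concerns people with psychiatric or substance use comorbidities, who will be in both randomized arms, and says nothing about a difference between A and B.

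A reader might also conclude that the trial has no sensitivity analysis. That cannot be said: this is a condensed article, and an analysis plan may exist that is not shown.

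Finally, if the sources of the 45% and 30% already counted dropouts as smokers, the reductions under equal loss are already in those rates and step 4 would count some loss twice. This caveat stands, and the article does not settle it. It does not rescue the assurance, because loss that differs between arms can still distort the comparison.

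**Conclusion.** The point holds against the assurance in the sample size section, not against the missing-data rule. The article expects loss to lower the quit proportion and treats the difference as unaffected. Under its own rule, that requires both equal loss and equal abstinence among those lost, and only the first is mentioned.

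The size depends on assumptions that the article does not supply. At 200 per arm and a 30% null, type I error runs from 5% (all dropouts smoke, or equal loss), through about 6% (5-point gap) and 7–10% (10–15 point gap, dropouts half as likely to be abstinent as stayers), to about 11–19% (the same gaps, equally likely). For a true 45% v 30%, loss of 20% in A and 10% in B cuts power from 87.5% to 49% when those lost resemble their arm. Equal loss of 20% cuts it to 75%, with a 12-point difference. Both power figures assume that the planning rates do not already count dropouts as smokers. The text should be corrected. It does not invalidate the primary analysis.

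**What to change.** Keep dropouts scored as smokers in the primary analysis. In Sample size calculations:

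1. Delete the statement that the difference should stay the same.
2. State whether the 45% and 30% already count dropouts as smokers, and the loss assumed in each arm. If they do not, restate power at 200 per arm with that loss included.
3. Tie the equal-loss condition to a tipping-point analysis of weeks 9–12 abstinence that varies the abstinence rate among those lost separately in A and B. Say that any positive claim will be reported with the point at which it tips. If the analysis plan already contains this, a pointer is enough.

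The cost is a few lines of text and a little programming, with no new data or participants. The downsides are a less favourable stated power and a positive result that may have to carry a qualification.

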### Study settings

Study settings include a smoking cessation treatment clinic at the Centre for Addiction and Mental Health (CAMH) in Toronto, Canada, and a smoking cessation treatment clinic at the University of Ottawa Heart Institute (UOHI) in Ottawa, Canada.

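### The primary unadjusted chi-square is valid but leaves out prognostic values recorded before randomised treatment, which gives up a modest amount of precision

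*Protocol article*

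**What the plan says.** The Statistical analysis section of the protocol article names one primary comparison: "The primary analysis will compare the proportions of patients in each group (group A vs group B) to achieve smoking cessation". The same sentence fixes the test: "to achieve smoking cessation using Pearson’s chi-square test". Participants who drop out count as smokers, so all randomised participants stay in the comparison.

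Adjustment enters in two other ways:

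- **Regression on prognostic variables:** "Additional analysis will employ logistic regression to adjust for variables known to be strongly associated with smoking cessation", with the list given as "including but not limited to age, sex, and psychiatric comorbidities".
- **Regression on imbalanced variables:** baseline characteristics are tested for significant differences between the randomised groups, and "Such variables will be used as covariates in an adjusted analysis".

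Under Sample size calculations, for 45% v 30%, "a sample of 163 per group provides 80% power to detect this difference", and the plan is to randomise 200 per group.

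The Initial assessment section has FTND, exhaled carbon monoxide, demographics and smoking history collected before the run-in. Under Titration phase, each weekly dose decision uses average cigarettes per day in the week before. At the week-3 visit that week belongs to the run-in, so the value precedes randomised treatment.

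**The concern.** The article itself describes its adjustment variables as strongly associated with cessation, yet keeps them out of the one comparison on which the trial will be judged. If they are as prognostic as that wording implies, part of the outcome variation could be removed from the A v B comparison at no cost in participants.

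The two adjusted analyses do not make up for this. One has a list that is not closed. The other chooses covariates by observed imbalance, which under randomisation is chance and says nothing about how well a variable predicts quitting. It also means that its model is settled only after the data are seen.

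At stake is the width of the primary confidence interval and some power. The validity of the primary result is not in question.

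**Working it through.** **Inputs from the article.** Rates of 45% (A) and 30% (B), alpha 0.05, 80% power, 163 per group needed, 200 per group planned, 1:1 allocation. Sidedness is not stated. **Assumed:** the prognostic strength of the covariates, since the article gives none.

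**Step 1: reproduce the stated sample size.** With mean rate 0.375 and pooled variance under the null,

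n = [1.960·√(2·0.375·0.625) + 0.8416·√(0.45·0.55 + 0.30·0.70)]² / 0.15²

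= (1.3419 + 0.5693)² / 0.0225 = 162.3, so **163**.

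The plan's figure is therefore that of an unadjusted two-sided comparison.

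**Step 2: unadjusted power at 200 per group.**

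Power = Φ[(0.15·√200 − 1.3419) / √0.4575] = Φ(0.7794 / 0.6764) = Φ(1.152) = **87.5%**.

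**Step 3: adjusted power by approximation.** If covariates explain a share R² of outcome variance, the effective size is about n/(1 − R²).

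| Assumed R² | Effective n per arm | Power | N per arm for 80% |
|---|---|---|---|
| 0 | 200 | 87.5% | 163 |
| 0.02 | 204 | 88.2% | 160 |
| 0.05 | 211 | 89.1% | 155 |
| 0.10 | 222 | 90.7% | 147 |

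A 12% variance cut gives 200/0.88 = 227 and 91.3%, a gain of 3.8 points.

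**Step 4: simulation with one known prognostic score.** 45% v 30%, 200 per arm, 3,000 trials per setting, chi-square v standardised risk difference:

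- No prognostic value: 88.1% v 88.0%.
- Odds ratio 1.5 per SD (R² 0.033): 88.0% v 88.5%.
- Odds ratio 2.0 per SD (R² 0.086): 88.0% v 90.5%. The standard-error ratio is 0.961, so variance falls by 1 − 0.961² = 7.6%.

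With a log-odds slope of 0.8 (4,000 trials), power went from 88.0% to 91.6% and variance fell by 12%.

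**Step 5: simulation with six estimated covariates**, closer to what would be fitted. 200 per arm, 4,000 trials per setting:

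| Discrimination of the six covariates | Change in variance | Change in power (points) |
|---|---|---|
| None | +2% | +0.6 |
| AUC 0.57 | +1% | +0.9 |
| AUC 0.59 | −1% | +1.3 |
| AUC 0.63 | −2% | +1.9 |
| AUC 0.70 | about −10% | +3.7 |

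A separate six-covariate run gave about 87% rising to 89.6% (slope 0.5, variance −4%) and 90.6% (slope 0.8, variance −10%).

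**Step 6: type I error.** In the six-covariate runs, null rejection with an uncorrected influence-function standard error was 5.2 to 5.4%, against 4.9 to 5.0% for the chi-square. So the apparent power gain at weak discrimination partly reflects a standard error that is slightly too small. By the Step 3 approximation, a true 2% rise in variance gives an effective size of 200/1.02 = 196 and power of 86.9%, a loss of about 0.6 points.

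**The case against.** The strongest defence is that nothing here is wrong. The chi-square is a valid, fully specified primary test, the sample size was computed for it, and 200 per group exceeds 80% power on the stated rates. Adjustment is already planned as additional analysis, and its exact list may be fixed in an analysis plan that is not shown. All of this stands, and it limits the point to efficiency. It does not remove it, because the article does fix the primary test as unadjusted.

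The size rests on assumption, and that stands too. Everyone randomised smoked at least 10 cigarettes a day at entry and failed the run-in, which may narrow the spread of dependence and smoking variables and so weaken them as predictors. With several weak covariates the gain is close to nil or slightly negative.

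The fitted model also needs complete covariates, whereas the chi-square keeps every randomised participant. That is a fair practical objection, and the fix has to include a rule for missing values.

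The objection that adjustment changes the question applies to a conditional odds ratio. A standardised risk difference is still the A v B difference in proportions.

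The spare power is also less secure than it looks. If, as an illustration, 20% of would-be abstainers in each arm were lost and counted as smokers, 45% v 30% would become 36% v 24%. Power at 200 per arm would then be 74.7%, or 76.8 to 79.0% with R² of 0.05 to 0.10.

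**Conclusion.** The point holds as lost efficiency. At the planned rates and 200 per arm, a covariate-standardised primary analysis would add roughly 1 to 4 points to a power of about 87.5% and cut variance by about 0 to 12%. The upper end needs covariates with an AUC of about 0.70 (a log-odds slope near 0.8). With useless covariates variance rises by about 2%. The article does not say where in this range the trial lies.

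A reader might infer more than the article supports:

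- **That the primary test is invalid or the trial underpowered by its own figures.** It is neither: 163 reproduces exactly, and 200 are planned.
- **That adjustment is absent.** It is planned, but not as primary.
- **That the plan leaves open which result counts.** It labels the chi-square primary and the regression additional. The open list affects only the supportive analysis.
- **That leaving out site is a fault.** The Study settings section names two clinics, one of them "a smoking cessation treatment clinic at the University of Ottawa Heart Institute (UOHI) in Ottawa, Canada", but nothing shows site to be prognostic, and the article mentions no stratification by it. Most of any gain would come from the smoking and dependence variables.

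**What to change.** Before unblinding, change the analysis wording as follows:

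1. Make the primary analysis the A v B risk difference, standardised over a logistic model with treatment and a short list fixed in advance: baseline FTND, baseline exhaled carbon monoxide, cigarettes per day in the week before the week-3 visit, age and sex. Site is optional.
2. Give a 95% confidence interval from a robust or influence-function standard error with a small-sample degrees-of-freedom correction, because the uncorrected version ran slightly above 5% under the null.
3. Impute missing baseline covariates by a simple rule that ignores arm, so that every randomised participant stays in the analysis. Keep dropout counted as smoking for the outcome.
4. Keep Pearson's chi-square as the supportive unadjusted result.
5. Drop the selection of covariates by baseline significance tests.

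**Cost:** no new data and no more participants, but slightly more analysis work and an amendment to the analysis wording. The Ethics and dissemination section sends protocol amendments to both research ethics boards and then to Health Canada. The article expects recruitment to run to January 2022, so at this version there is still time.

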#### Analysis of secondary and tertiary outcomes

The proportion of patients who remain abstinent from week 9 to weeks 26 and 52 will be compared by logistic regression, weighted by the inverse probability of being included in the subset. Exploratory analysis of the role of nicotine metabolism on quit outcome will be performed: (1) initial analysis will compare the proportions of patients with rapid or slow NMR who achieve the primary outcome within each treatment group using a chi-square; (2) we will then conduct a post hoc analysis of NMR as a predictor or moderator of treatment outcome in the two treatment groups; and (3) an exploratory analysis of the correlation between final NRT dose given and NMR.

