### Randomization

After the 2-week run-in phase, stage 2 will be initiated, in which participants who fail to achieve 7-day abstinence (self-report of not smoking for at least the past 7 days at week 3 study visit) will be randomly assigned to the experimental (group A, escalating active patches) or a control condition (group B, escalating placebo patches) for 10 additional weeks of treatment. To maintain allocation concealment, participants will be randomized 1:1 in permuted blocks of varying sizes. The randomization schedule will be generated by the research pharmacist under guidance of the co-investigator statistician and stored securely in the pharmacy. Only the research pharmacists will be unblinded to group assignment. Participants, investigators, and research staff will be blind to group A or B assignment. Participants who stop smoking during the run-in phase will not be randomized but instead will continue with an open-label nicotine patch 21 mg/day (group C) for another 10 weeks. We estimate that 20% of participants will be able to quit smoking in the first 2 weeks to comprise group C. This group will be used to test some of the exploratory hypotheses outlined above.

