#### Secondary outcome measures

The secondary outcome measures are self-reported continuous abstinence through week 9 to weeks 26 and 52, confirmed by urinary cotinine < 200 ng/ml (assay limit of detection) at the 26- and 52-week follow-up visits.

To test the hypothesis that rates of nicotine metabolism moderate the effect of patch titration, we will compare the quit outcomes in rapid versus slow nicotine metabolizers within and among the treatment groups.

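### The week 26 and 52 abstinence analysis is weighted to an undefined subset, which conflicts with the statement that all randomised participants are analysed

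*Protocol article*

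**What the plan says.** All references are to the protocol article.

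- **Secondary outcome measures** defines the long-term outcome as "self-reported continuous abstinence through week 9 to weeks 26 and 52", confirmed by urinary cotinine at those two visits.
- **Analysis of secondary and tertiary outcomes** says the proportion who remain abstinent "will be compared by logistic regression, weighted by the inverse probability of being included in the subset". Neither this section nor any other says which subset is meant or how inclusion is modelled.
- **Sample size calculations** plans for 45% abstinent in group A in weeks 9–12; the rates "for group B are 30% based on published literature". On that basis "a sample of 163 per group provides 80% power to detect this difference at weeks 9 through 12". It then gives 200 per group as enough for the longer-term outcomes too. The next sentence reads "Since we are using ITT, all participants randomized to a treatment arm will be included in the analysis" and adds that n will not change. Losses to follow-up are described as lowering the proportion counted as quit.
- **Statistical analysis** counts dropouts and losses as still smoking, but that sentence is worded for the primary analysis only.

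**The concern.** A subset whose inclusion probability has to be modelled is not everyone randomised, and n is not constant in it. The two sections also handle losses differently. In the sample size text a loss pulls the quit rate down. In a weighted analysis a loss is replaced by up-weighting similar people who were included, and the quit rate need not fall.

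The outcome definition adds to the difficulty. Abstinence must run unbroken from week 9, so a participant who smoked in weeks 9–12 has failed the week 26 and week 52 outcomes whether or not they attend. Those people need no weighting and should not leave the denominator.

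At stake are the only long-term efficacy comparisons that the article specifies, which are also its stated reason for randomising 200 rather than 163 per group. Depending on what the subset turns out to be, the estimate may or may not describe the groups as randomised. Because the word is left open, that choice could be made after the data are seen.

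**Working it through.** **1. The plan's own figure.** Inputs from Sample size calculations: 45% v 30%, alpha 0.05 (taken as two-sided), 80% power; 1:1 allocation from Randomization. With pooled variance, p̄ = 0.375 and no continuity correction:

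n = [1.96·√(2·0.375·0.625) + 0.8416·√(0.45·0.55 + 0.30·0.70)]² / 0.15² = (1.342 + 0.569)² / 0.0225 ≈ 162.3, so 163 per group. The stated figure reproduces. Power at 200 per group is 87.5% for the weeks 9–12 outcome.

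**2. Who has an unobserved long-term outcome.** Expected weeks 9–12 abstainers: 0.45 × 200 = 90 in A and 0.30 × 200 = 60 in B. The remaining 110 and 140 (250 of 400) are known failures. At most 150 people can have an unobserved outcome at week 26 or 52.

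**3. Reading 1: the subset is the weeks 9–12 abstainers.** The article gives no long-term rates, so retention among these abstainers is assumed. The all-randomised rate is the weeks 9–12 rate times retention; OR = [p_A/(1−p_A)] / [p_B/(1−p_B)].

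| Assumed retention A v B | All randomised (200 v 200) | OR | Subset (90 v 60) | OR |
|---|---|---|---|---|
| 50% v 50% | 22.5% v 15.0% | 1.65 | 50% v 50% | 1.00 |
| 45% v 50% | 20.3% v 15.0% | 1.44 | 45% v 50% | 0.82 |
| 40% v 50% | 18.0% v 15.0% | 1.24 | 40% v 50% | 0.67 |
| 50% v 45% | 22.5% v 13.5% | 1.86 | 50% v 45% | 1.22 |

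First row: (0.225/0.775)/(0.15/0.85) = 0.2903/0.1765 = 1.65. Third row: (0.18/0.82)/(0.15/0.85) = 1.24, against (0.40/0.60)/(0.50/0.50) = 0.67. The subset comparison measures relapse among early quitters and leaves out the difference in how many quit. The analysed number falls from 400 to about 150.

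**4. Reading 2: the subset is those who attend follow-up.** Assume true rates of 22.5% v 15%, 90% attendance among abstainers, and weights that carry no information on outcome-related attendance. The rate among attendees is p·0.9 / [p·0.9 + (1−p)·s], where s is attendance among smokers.

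- s = 60% in both arms: A 0.2025/0.6675 = 30.3%; B 0.135/0.645 = 20.9%; OR 1.65. Counting missing as smoking gives 20.3% v 13.5%, OR 1.63. The odds ratio is hardly affected, although both rates are inflated.
- s = 80% in A, 40% in B: A 0.2025/0.8225 = 24.6%; B 0.135/0.475 = 28.4%; OR 0.82. Counting missing as smoking still gives OR 1.63.

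Under reading 2, a reversal therefore needs a large difference between arms in smokers' attendance that the weights fail to capture.

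**The case against.** The strongest defence is that inverse-probability weighting is a standard tool for incomplete follow-up. On that view the subset most naturally means people with week 26 or 52 data, and remaining abstinent from week 9 simply restates the continuous outcome. Correctly specified weights aim to recover the all-randomised comparison. A journal article may leave the subset definition and weight model to fuller documents, and the all-randomised sentence sits in sample size text that speaks of one analysis. Only secondary outcomes are affected.

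Much of this stands. The missing definition alone is not a finding, and under the attendance reading bias is not automatic. What survives is the conflict: the sentence on including everyone with constant n directly follows the one on longer-term outcomes, and no later definition of a subset with inclusion probability below 1 makes the two agree. Weighting attendees also drops known weeks 9–12 failures who do not attend.

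Three stronger conclusions are tempting but not supported:

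- *The weighted analysis breaks the missing-counts-as-smoking rule.* That rule is worded for the primary analysis, so a different method for secondary outcomes does not contradict it.
- *The analysis will remove or reverse the treatment effect.* This depends on which subset is meant and on retention or attendance rates that the article does not give.
- *The weights use baseline data only and so cannot work.* The article does not state the weight model.

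Nor is the outcome observed for all 400. An abstainer who misses follow-up has no report and no cotinine result, and scoring that person as a smoker is an imputation.

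**Conclusion.** The long-term analysis is wrong as written, because weighting to an undefined subset cannot be reconciled with including all randomised participants at constant n. That conclusion needs no assumption about rates.

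The size of the harm is conditional. If the subset is the weeks 9–12 abstainers, equal retention is enough to turn an all-randomised odds ratio of 1.65 into 1.00, and retention five to ten points lower in A reverses the direction (1.44 to 0.82; 1.24 to 0.67). These figures use the article's 45% and 30% with assumed retention. If the subset is follow-up attendees, the odds ratio is little changed when smokers attend equally in both arms. It reverses only under a marked attendance difference, such as the assumed 80% v 40%, that the weights miss. The primary weeks 9–12 comparison is not affected.

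**What to change.** Replace the sentence on weeks 26 and 52 in Analysis of secondary and tertiary outcomes with text to this effect:

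> Continuous abstinence from week 9 to week 26 and to week 52 will be compared between groups A and B in all randomised participants by logistic regression. Anyone not abstinent in weeks 9–12, or missing at the follow-up visit, will be counted as not abstinent. As a sensitivity analysis, missed follow-up among weeks 9–12 abstainers will be handled by inverse-probability weighting, with weeks 9–12 failures kept in the denominator as failures and the variables in the weight model listed.

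This brings the section into line with the sample size text and the primary analysis. It costs one paragraph and needs no new data or visits. The article describes the trial as still recruiting, so as of that date the change could precede any analysis.

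There are two limits. Counting missing as smoking remains an imputation for abstainers who miss follow-up, which is why the weighted analysis is worth keeping. The change also does not secure long-term power: at the illustrative 22.5% v 15%, 200 per group gives 48.5%.
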